## Abstract

**Background:**

Autism spectrum disorder (ASD) is a developmental impairment characterized by persistent deficits in social communication and interactions, and over half of children with ASD possess below average intellectual ability (IQ < 85). The social development and response to social skill interventions among children with ASD and comorbid intellectual disability (ID) is not well understood. Music therapy is a systematic process of intervention, wherein a therapist may help clients promote their social skills by using musical experience. The proposed study will address limited research evidence on music therapy as an intervention for social functioning in children with ASD with mild to borderline ID.

**Method:**

A randomized controlled trial (RCT) with two parallel groups of 40 children each (1:1 allocation ratio) is planned. Participants will receive 45 min of music therapy or non-musical intervention targeting social skills once a week for 12 weeks. Primary outcome measures will be independent ratings on the Childhood Autism Rating Scale and parent ratings on the Social Responsiveness Scale-2. Linear mixed-effects models for these two outcome measures will be created for data collected at 2-week pre-intervention, 2-week post-intervention, and 4-month post-intervention sessions. In-session behaviors at the first and last intervention will be videotaped and coded offline and compared. Pretreatment neural response of quantitative electroencephalograms (qEEG) to social scenes will be used to predict the outcomes of musical and non-musical social skill interventions, whereas qEEG responses to music will be used to predict the effectiveness of musical social skill intervention.

**Discussion:**

If neural markers of social skill development are found, then the long-term goal is to develop individualized intervention based on pre-treatment markers to maximize treatment efficacy. The proposed study’s results may also suggest directions to development and provision of music therapy services in Hong Kong.

**Trial registration:**

ClinicalTrials.gov (NCT04557488). Registered September 21, 2020.

## Background

Autism spectrum disorder (ASD) is a developmental impairment characterized by persistent deficits in social communication and interactions coupled with restricted and repetitive patterns of behaviors. The symptoms of ASD appear in early childhood. The prevalence of childhood ASD in the Greater China Region is 26.6 per 10,000 children [1], but the figures have increased rapidly in recent years due to the expansion of diagnostic criteria and increased public awareness. Given that no known cure or effective pharmacological intervention for ASD is available, behavioral interventions that target autism symptoms is the main strategy to support individuals with ASD to be integrated into school and the society. Intervention studies typically target the core social deficits in ASD, including low inclination for human interactions, lack of social skills, and impairments in interpersonal communication. Social skill training may cover a myriad of social behavior, including initiating interaction, responding, maintaining eye contact, using appropriate co-speech gestures, and conversational turn-taking. Training for high-level social cognition may involve understanding non-literal language, perspective taking, and recognizing emotions [2].

Although high-functioning ASD individuals do not tend to naturally comprehend social conventions, they can follow established rules and imitate modeled social behavior. However, the effectiveness of explicit social skill training may not generalize to low-functioning school-aged children with ASD. Explicit training is likely to be less effective for children with severe autistic symptoms who actively avoid social interactions or who may demonstrate limited intellectual ability. The clinical presentations of ASD vary to a large extent, and approximately 56% of children with ASD possess below average intellectual ability (IQ < 85) [3]. The intellectual, verbal, and social ability in this population may greatly influence intervention outcomes. The social development of children with ASD and comorbid intellectual disability (ID) is not well understood, and systematic investigations on how children with ASD and ID respond to social skill interventions remains to be done.

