Frontal alpha asymmetry (FAA) is typically investigated in relation to emotional response and motivations, both in clinical and normal populations [10]. Left-lateralized or left-dominant brain activity has been linked to an *approach* system where an individual experiences positive emotions and motivations. In contrast, right-lateralized frontal activity may reflect negative emotions and intention to withdraw. Reduced alpha power in the left frontal area of the scalp in individuals with ASD has also been reported [9]. The modulation of FAA has been demonstrated in neurofeedback training in individuals with ASD to activate their imitation behaviors [11, 12], so this measure is hypothesized to predict and be responsive to social skill interventions. High-functioning individuals with ASD show intact emotional processing when listening to music, although they demonstrate distinct neural patterns relative to neurotypical adults, which is interpreted as increased cognitive load and physiological arousal [13]. Individual preference for music varies within the target group with ASD and ID and may predict how they respond to social skill intervention using music therapy. Although self-report rating scales exist for reporting music experience and preference, qEEG measures may be superior because they index automatic responses to musical stimuli that the target population of children with ASD and ID may find difficult to understand or express.

The proposed study will address the research gap on music therapy as an intervention for social functioning in children with ASD with mild to borderline ID. The research design is to examine whether using music therapy as social skill intervention provides additional benefits relative to non-musical active control behavioral intervention in a 12-week RCT. We will also evaluate whether pre-treatment neural response to music is correlated with the effectiveness of musical social skill intervention. If correlation is found, then the long-term goal is to develop individualized intervention based on pre-treatment markers to maximize treatment efficacy.

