### Objectives

Aims and hypotheses to be tested:
On the group level, is social skill intervention using music therapy more effective in enhancing social interaction than non-musical social skill training for children with ASD and co-occurring mild/borderline ID?On the individual level, are participants with enhanced left-lateralized FAA to social scenes relative to baseline more responsive to both types of social skill interventions?For participants in the music therapy intervention, does enhanced left-lateralized FAA to preferred music relative to baseline predict better outcomes in social skill development?

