### Inclusion and exclusion criteria

The inclusion criteria include a formal clinical diagnosis of ASD and an assessed overall and verbal IQ of 50–84 by a certified clinician. Children who report hypersensitivity to sounds will be included with consent but will be withdrawn immediately if adverse reactions that cannot be controlled (e.g., screaming, attempts at self-harm) are observed. Intervention trainers, assistants, or parents of participants will be encouraged to report any adverse events to facilitate timely response.

Children who exhibit severe physical or sensory disabilities (e.g., deafness) that may limit their participation in either intervention will be excluded. Children with other neurodevelopmental, psychiatric, or neurological comorbidities or are on prescribed psychiatric medication will also be excluded from the study. Children who already engage in music therapy or other social skill interventions (excluding standard care) will be ineligible to enroll in the study.

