##### Emphasis of approach

The trainer will typically focus on building a relationship with the participants, understanding their current levels of functioning, and choosing musical activities that may scaffold their social development.

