##### Emphasis of approach

Focus is typically on explicit and concrete instructions, reinforcing good social habits, and fostering positive associations for group interactions. Musical activities will be excluded in this control condition to contrast the specific effects of music therapy in intervention. This type of group training is typically offered by schools or NGOs in Hong Kong for children with ASD with or without ID, and may be considered as a standard practice control condition relative to music therapy targeting social skills.

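### The control section says dropping music shows the specific effects of music therapy, but the arms also differ in teaching emphasis, so a positive Aim 1 supports the programme and not music itself

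*Protocol article*

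**What the plan says.** **Purpose of the control.** Under Control group intervention, Emphasis of approach, the protocol article says: "Musical activities will be excluded in this control condition to contrast the specific effects of music therapy in intervention". The same paragraph adds that such training is usual locally and may be regarded as a standard-practice comparator.

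**Teaching emphasis by arm.** For the control: "Focus is typically on explicit and concrete instructions, reinforcing good social habits, and fostering positive associations for group interactions". For the music arm, under the parallel heading: "The trainer will typically focus on building a relationship with the participants, understanding their current levels of functioning", followed by the choice of musical activities that scaffold social development.

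**What the Background expects.** It says that "the effectiveness of explicit social skill training may not generalize to low-functioning school-aged children with ASD". It continues: "Explicit training is likely to be less effective for children with severe autistic symptoms who actively avoid social interactions", and the same sentence also names limited intellectual ability.

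**Who is enrolled.** Eligibility requires "an assessed overall and verbal IQ of 50–84 by a certified clinician".

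**The question.** Aim 1 in Objectives asks: "is social skill intervention using music therapy more effective in enhancing social interaction than non-musical social skill training". The end of the Background puts it as "whether using music therapy as social skill intervention provides additional benefits relative to non-musical active control behavioral intervention".

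**Measurement.** In-session social behavior plans to take trainer talking time (as the measure of explicit instruction) and amount of music from the video. These are fidelity data that may become covariates if they differ significantly between groups.

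**The concern.** A contrast shows the specific effect of an ingredient only if that ingredient is what separates the arms. Here at least two things separate them by design: whether music is used, and how far teaching relies on explicit instruction. The Background gives a reason to expect the second to matter in this population, and in a direction that disadvantages the control.

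What is at stake is the reading of a positive result. The Discussion looks ahead to music as a cheap, scalable element for school programmes and curricula. If the gain came from a less explicit style of teaching, adding music to a curriculum would not reproduce it.

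**Working it through.** **1. The arms side by side**

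| Feature | Music arm | Control arm |
|---|---|---|
| Schedule | 45 min weekly, 12 weeks | same |
| Group size | 8 | 8 |
| Target skills by session pair | vocalisation, choice and sharing, social cues, initiation and turn-taking | largely the same |
| Music | yes | excluded |
| Stated emphasis | relationship building, scaffolding | explicit and concrete instruction |
| Techniques | songs, instruments, improvisation | modelling, games, crafts, social stories, role-play, explicit instruction or demonstration with feedback |
| Trainer | one music therapist | one social worker |

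Schedule, group size and target skills are matched. Music, stated emphasis and trainer are not. Taking the songs out of the music arm would not yield the control.

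**2. Does the protocol expect emphasis to matter?** The Background says explicit training may not carry over to low-functioning children and links lower effectiveness to limited intellectual ability. Eligibility (IQ 50–84) falls wholly within the range that the Background calls below average (under 85). So the text gives a reason to expect a weaker control response, separate from any effect of music.

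**3. Can the planned covariates separate the two?** There are 80 / 8 = 10 groups, 5 per arm. Adding a group-level covariate x multiplies the variance of the arm effect by 1 / (1 − r²), where r is the correlation of x with arm across groups. If mean talking time differs between arms by g within-arm SDs (g is assumed; the documents give none), the between-arm sum of squares is about 10 × (g/2)² = 2.5g², the within-arm sum is about 8, and the factor is roughly 1 + 2.5g²/8.

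| g | Approximation | Simulated median |
|---|---|---|
| 2 | 2.25 | about 2.3 |
| 3 | 3.81 | about 4.0 |
| 5 | 8.81 | about 9.5 |

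Precision is the lesser problem. Talking time and music use are consequences of the assigned programme, measured after randomisation. Adjusting for them removes part of the effect that Aim 1 asks about and does not leave an effect of music.

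**4. Illustration of size**

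The plan's own figure first: for d = 0.71, α = 0.05 and power 0.8, a two-sided t-test needs 32.1, so 33 per group before attrition. This reproduces the stated 33, but the point does not depend on it. For the numbers analysed I use the planned 40 per arm and 40 × 0.75 = 30 after the stated 25% attrition.

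Assume music adds nothing and teaching style alone gives a difference d. The power of a two-sided 5% t-test comes from the noncentral t distribution with noncentrality d√(n/2) and 2n − 2 degrees of freedom. For d = 0.35:

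- n = 30: 0.35 × √15 = 1.356, 58 df, critical value 2.002; power 0.266.
- n = 40: 0.35 × √20 = 1.565, 78 df, critical value 1.991; power 0.340.

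| Assumed d | 30 per arm | 40 per arm |
|---|---|---|
| 0.20 | 12% | 14% |
| 0.35 | 27% | 34% |
| 0.50 | 48% | 60% |

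The calculation follows the two-group t-test of the sample size section and ignores clustering by therapy group.

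**The case against.** The other side has real strength.

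- **Aim 1 is already a programme comparison.** It sets music therapy against non-musical training, and the comparator is also called standard practice. This stands: Aim 1 is answerable and needs no rewording.
- **Relationships belong to music therapy.** The section on use of music defines the therapy to include relationships developing through musical experience, so relationship building is not a contaminant. This stands for the therapy as a package. It does not account for the control's explicit emphasis, and the Discussion speaks of music, not of the package.
- **The Discussion is conditional.** It requires positive results and also that mechanisms be identified. This stands as a partial safeguard, but the design offers no contrast that would separate music from teaching approach.
- **The arms are closer than the emphasis statements suggest.** Both say that the focus is typical, the control includes games, crafts and role-play, and target skills are largely matched. This narrows the difference without removing it.
- **The Background compares populations, not teaching styles.** It does not say that relationship-based teaching without music would do better. This stands: the handicap is an expectation drawn from the text, not a stated forecast for these arms.

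A reader might infer that the control claims to isolate music, that Aim 1 is therefore invalid, or that the percentages above are false-positive rates. The documents support none of these. The control section speaks of a contrast, Aim 1 compares programmes, and under that aim a real difference caused by teaching style is a true positive.

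**Conclusion.** The point holds as a limit on attribution. The arms differ in teaching emphasis as well as in music, the Background gives a reason to expect that difference to favour the music arm, and no planned analysis separates the two. A positive Aim 1 would support the music therapy programme over explicit behavioural training. It would not show that music is the active part, as the control rationale and the Discussion imply.

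The size cannot be taken from the documents, which give no teaching-style effect. With an assumed d = 0.35, the chance of a significant programme difference to which music contributed nothing is about 27% to 34%. It is lower or higher as that assumption moves. Randomisation and the validity of the Aim 1 comparison are not affected.

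**What to change.** 1. In the control's Emphasis of approach, replace the specific-effects rationale with a plain statement that the music therapy programme is compared with standard-practice explicit behavioural social skill training.
2. State in advance that any difference will be attributed to the programme and not to music as opposed to teaching approach, and make the Discussion's remarks on music in curricula subject to this.
3. Report trainer talking time and music use by arm descriptively, and keep them out of the Aim 1 model as covariates.

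The cost is some rewording and one table from video data already planned. No participants, assessments or intervention content change. The downside is a narrower claim.

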### Use of music in social skill intervention

The choice to examine music in social skill intervention is motivated by accruing evidence of its potential for therapeutic use for various clinical populations [4]. The use of music in ASD intervention is quite common. Background music may be used to increase familiarity and relaxation, whereas active music activities can provide a point of contact between instructors and children with ASD, thereby helping to build rapport and promote learning through non-verbal interactions [4, 5]. However, music therapy as social skill intervention for low-functioning ASD individuals have not been comprehensively examined. For ASD intervention, music has been explored as a medium to increase social skills in the field of music therapy for some years [5]. Music therapy is defined as a systematic process of intervention, wherein a therapist helps clients promote their health by using musical experience and relationships that develop through them [6]. Children with ASD and ID are often described as preoccupied in their own world and may be highly passive or unresponsive in social situations. The low verbal ability of these children is one limitation to their participation given that social interactions often involve verbal exchanges. Music may become a conduit for children whose natural affinity to social interactions is impaired because group music making and improvisations encourage initiation and turn-taking behavior in a non-verbal situation. In group music therapy, children with ASD can learn to tolerate the presence of and physical contact with other people, distinguish between oneself and others, and practice social behavior [5, 6].

A Cochrane review in 2014 analyzed behavioral data from 10 RCT studies comparing music therapy with non-musical placebo therapy or standard care [7]. The results demonstrated moderate-quality evidence supporting the effectiveness of music therapy in improving social interactions and initiating behavior, social adaptation, and parent–child relationship. No adverse effects have been reported. Although flaws in study designs and low numbers of participants in some studies have precluded strong conclusions, available evidence indicates that music therapy improves social–emotional reciprocity and verbal and nonverbal communicative skills outside the context of therapy. By contrast, a recent large-scale multicenter RCT study on music therapy for 364 children with ASD aged 4–7 years has found no significant differences in social skills compared with standard care as measured by clinical observations or parental ratings [8]. These mixed findings may be due to the heterogeneity of the studies, which involved children belonging to different age groups, abilities, and living in different countries. Long-term outcomes are also unclear in these studies. Since effectiveness of clinical interventions is influenced by social and cultural contexts [6], previous studies must be replicated and extended to obtain locally relevant data. The proposed study will contribute to a clear evidence base that serve to inform and develop music therapy in social skill interventions for children with ASD and ID in Hong Kong.

### Prediction of treatment success

One hypothesis that has not been tested in previous studies is that success in social skill interventions may depend on individual differences. Autistic symptoms and abilities vary widely among children with ASD, arising both from different developmental speeds and specific interests. Some individuals may possess deficits in the areas of restricted interests or repetitive behavior, which results in poor social skills; however, they are accepting of social interactions. The willingness to seek out social experiences is the foundation to social skill development because without initial interests in social behavior, the motivation to attend to the explicit training and modeling is low. In such cases of social avoidance, cultivation of social interests through other strategies, such as music making, may be more effective. Narrowing down the characteristics of children who respond well to a particular type of intervention can facilitate timely and efficient treatment provision. To build the foundation for an evidence-based strategy for individualizing treatment plans, research should explore markers that indicate responsiveness to interventions. In this study, we propose to test quantitative electroencephalogram (qEEG) signals in response to music and social scenes as predictive measures of treatment outcomes.

Spontaneous electrophysiological neural activities at rest or when engaged in task can be measured by qEEG. Spectral analysis is used to decompose qEEG signals across several minutes into different frequency bands, which are associated with specific functions. The most consistent pattern of findings in the literature is that individuals with ASD show a U-shaped pattern of spectral power relative to controls without ASD [9]; that is, excessive power is observed at low-frequency (delta, 1-3 Hz and theta, 4–7 Hz) and high-frequency (beta, 13-35 Hz and gamma, > 35 Hz) bands, but reduced power is detected in middle-range frequency band (alpha, 8-12 Hz). The pattern was found with wide topographic distribution, which suggested abnormalities across multiple brain regions. This finding was reported for children in different age groups and for individuals with or without comorbid ID. High-frequency bands have been associated with emotional responses and emotion recognition and may be linked to such deficits in individuals with ASD. Neural patterns that deviate from age-matched controls to a greater extent may suggest more severe behavioral symptoms.

Frontal alpha asymmetry (FAA) is typically investigated in relation to emotional response and motivations, both in clinical and normal populations [10]. Left-lateralized or left-dominant brain activity has been linked to an *approach* system where an individual experiences positive emotions and motivations. In contrast, right-lateralized frontal activity may reflect negative emotions and intention to withdraw. Reduced alpha power in the left frontal area of the scalp in individuals with ASD has also been reported [9]. The modulation of FAA has been demonstrated in neurofeedback training in individuals with ASD to activate their imitation behaviors [11, 12], so this measure is hypothesized to predict and be responsive to social skill interventions. High-functioning individuals with ASD show intact emotional processing when listening to music, although they demonstrate distinct neural patterns relative to neurotypical adults, which is interpreted as increased cognitive load and physiological arousal [13]. Individual preference for music varies within the target group with ASD and ID and may predict how they respond to social skill intervention using music therapy. Although self-report rating scales exist for reporting music experience and preference, qEEG measures may be superior because they index automatic responses to musical stimuli that the target population of children with ASD and ID may find difficult to understand or express.

The proposed study will address the research gap on music therapy as an intervention for social functioning in children with ASD with mild to borderline ID. The research design is to examine whether using music therapy as social skill intervention provides additional benefits relative to non-musical active control behavioral intervention in a 12-week RCT. We will also evaluate whether pre-treatment neural response to music is correlated with the effectiveness of musical social skill intervention. If correlation is found, then the long-term goal is to develop individualized intervention based on pre-treatment markers to maximize treatment efficacy.

